## 5. Discussion

Pelvic floor rehabilitation is becoming more and more important due to the rapid development of rehabilitation medicine and the improvement of the life quality of demanded by women. PFMT is one of the widely adopted exercise therapies in the clinic for female pelvic floor rehabilitation.

Although medical societies realize that rehabilitative exercises to be the currently demonstrated effective way to improve PFM, consensus on the standard for PFMT is still lack. Many issues are remaining; questions, such as “what is the right to exercise correctly?” and “what is the proper frequency and duration for PFM training?”, and reports on the efficacy of PFMT are much confusing. Due to the positional particularity and abstractness of pelvic floor muscles, it is difficult for a non-medical backgrounded woman to exercise pelvic floor muscle fiber I and fiber II directly, accurately, and/or effectively. PFMT has not been skilled for public populization, although many investigators have efforted exploring more convenient and effective pelvic floor rehabilitation methods.

In referring to comprehensive literature related to our previous research [20], we developed 12-week PEFLOW, with emphases on training of the entire muscle system. 

PEFLOW is composed of 10 sections as shown in Table 1. The warm-up section was setup to have the participants percept the pelvic floor contractions in different body positions via self-feeling to the pelvic floor movements. In this section, participants are instructed to practice quick contraction (1”) and relaxation (2”) for perception of type II muscle fiber (fast-twist fiber) and hold-on contraction (8-10”) and relaxation (8-10”) for perception of type I muscle fibers (slow-twist fiber). The training of multiple repetitions for fast-twist fibers is also a way of targeting slow-twist fiber [41]. Section 1 was integrated in the program to train the pelvic contractions corelating to the movements of standing, heel lifting, single feet standing, and walking. According to the literature, feet play roles in control and adjustment of postures, and exercises corelated with the movement of feet can improve body balance and simulate feedback perception [42]. Section 2 was setup to improve the flexibility and mobility of the lumbar vertebrae and pelvic, so as to make them adapt the changes in woman’s body postures that is the unavoidable outcome of pregnancy and delivery due to the changes in lumbar vertebrae bulge, pelvic width and tilt, and the relevant muscle tension [43]. With Section 3, we tend to train the movements of PFM with correlating to breaths. It was programed based on a rational from multiple studies that exhaling maximizes PFM tension and strength [14,44]. Sections 4–8 were programed to train joint contractions of the core muscles, surrounding muscles and PFMs as what more and more scientific evidence demonstrated that PFM contraction can be optimized by joint contractions of the core muscles such as abdominal, lumbar dorsal, and diaphragm muscles [40], and surrounding muscles such as hip abductors [45,46].

Optimal and long-term therapeutic effects are anticipated. We made PEFLOW be performed at home due to the meeting restrictions in COVID-19 pandemic. However, we anticipate that home exercise with the facilitation of online guidance and encouragement will increase the participation rate and the concordance of the women in taking correct exercise. The requirement for participants to report the RPE score after each training session is not only an encouragement to the participants, but a guarantee of the appropriate training intensity being kept training effectively and safely [47].

The possible limitation of this trial might be that we lack more precise measurements for physical activity level, such as wrist or waist accelerometers to monitor heart rate during daily physical activities and trainings.

## 6. Conclusions

In conclusion, this study is expects that the 12-week online PEFLOW is a cost-effective training for the recovery of Pelvic floor muscle function, which is suitable for future clinic trails and also for clinical promotions.

## Figures and Tables

**Figure 1 ijerph-19-11073-f001:**
[figure not shown]
Flowchart of the trial.

**Table 1 ijerph-19-11073-t001:** The 12-week Pelvic Floor Workout and the sectioning.

	Week	8-Scetion Program	Week	8-Scetion Program
**Warm-ups**	Pelvic floor perception, try to feel the contraction of pelvic floor muscles at different positions, including standing, lying and sitting position.			
**Main** **Progressive Exercises**	1	Standing squeezing Sitting on Swiss ball: pelvic dancing Lying: new respiratory exercise Lying: hip curling Lying: dynamic hand-knee resistance Side lying: knee bending side bridge Lying: alternating knee extension Four-foot kneeling: alternating knee extension	7	Walking squeezing Sitting on Swiss ball: pelvic with up-limb dancing Lying: new respiratory exercise with balloon Lying: hip isometric curling with balloon Lying with neck bending: leg clip ball+ isometric hand-ball resistance Side lying: knee extension isometric side bridge Lying: four-foot dynamic extension with elastic belt Four-foot kneeling: four-foot dynamic extension with elastic belt
	2	Standing squeezing Sitting on Swiss ball: pelvic dancing Lying: new respiratory exercise Lying: hip curling Lying: dynamic hand -knee resistance Side lying: knee bending side bridge Lying: four-foot dynamic extension Four-foot kneeling: four-foot dynamic extension	8	Walking squeezing Sitting on Swiss ball: pelvic with up-limb dancing Lying: new respiratory exercise with balloon Lying: Hip isometric curling with balloon Lying with neck bending: leg clip ball+ isometric hand-ball resistance Side lying: knee extension isometric side bridge Lying: four-foot dynamic extension with elastic belt Four-foot kneeling: four-foot isometric extension with elastic belt
	3	Calf raising squeezing Sitting on Swiss ball: pelvic dancing Lying: new respiratory exercise Lying: Hip curling Lying with neck bending: dynamic hand -knee resistance Side lying: knee bending “clam” side bridge Lying: four-foot dynamic extension Four-foot kneeling: four-foot dynamic extension	9	Walking squeezing +Arm large swing Sitting on Swiss ball: pelvic with up-limb dancing using elastic belt Lying: new respiratory exercise with balloon Lying: hip isometric curling with balloon Lying: neck bending +Leg Clip Ball+ Side ball shot Side lying: knee extension side bridge with arm cross swing Lying: four-foot dynamic extension with elastic belt Four-foot kneeling: four-foot isometric extension with elastic belt
	4	Calf raising squeezing Sitting on Swiss ball: pelvic dancing Lying: new respiratory exercise Lying: hip curling with balloon Lying with neck bending: dynamic hand -knee resistance Side lying: knee bending clam side bridge Lying: four-foot isometric extension Four-foot kneeling: four-foot isometric extension	10	Walking squeezing +Arm large swing Sitting on Swiss ball: pelvic with up-limb dancing using elastic belt Lying: new respiratory exercise with balloon Lying: hip dynamic curling with Swiss ball and balloon Lying with neck bending: Leg Clip Ball+ Side ball shot Side lying: knee extension side bridge with arm cross swing Side Lying: Four-foot isometric extension with elastic belt Four-foot kneeling: four-foot isometric extension with elastic belt on unstable support
	5	Single leg squeezing Sitting on Swiss ball: pelvic and up-limb dancing Lying: new respiratory exercise Lying: hip curling with balloon Lying with neck bending: isometric hand -knee resistance Side lying: knee extension dynamic side bridge Lying: four-foot isometric extension Four-foot Kneeling: four-foot isometric extension	11	Walking squeezing with arm small swing Sitting on Swiss ball: pelvic with up-limb dancing using elastic belt Lying: new respiratory exercise with balloon Lying: hip dynamic curling with Swiss ball and balloon Lying with neck bending: leg clip ball+ side ball shot Side lying: four-foot extension side bridge Lying: four-foot isometric extension with elastic belt Four-foot kneeling: four-foot isometric extension with elastic belt on unstable support
	6	Single leg squeezing Sitting on Swiss ball: pelvic and up-limb dancing Lying: new respiratory exercise Lying: hip curling with balloon Lying with neck bending: isometric hand -knee resistance Side Lying: knee extension dynamic side bridge Lying: four-foot isometric extension Four-foot Kneeling: four-foot dynamic extension with elastic belt	12	Walking squeezing with Arm small swing Sitting on Swiss ball: pelvic with up-limb dancing using elastic belt Lying: new respiratory exercise with balloon Lying: hip dynamic curling with Swiss ball and balloon Lying with neck bending: leg clip ball+ side ball shot Side lying: four-foot extension side bridge with upper leg abducted (if not, the same as week 11th) Lying: four-foot isometric extension with elastic belt Four-foot kneeling: four-foot isometric extension with elastic belt on unstable support
**Cooling Down**	Dynamic stretching, including upper and lower limbs, waist, back, and abdomen stretching and pelvic floor muscle relaxation with mini foam axis.			

**Table 2 ijerph-19-11073-t002:** Data collection and follow-up instruments.

		EG	CG	EG	CG	EG	CG
Baseline screen, Informed consent, Randomization							
The follow-up visits		The First		The Second		The Third	
Demographic data collection		◯	◯				
The MOS		●	●	●	●	●	●
POP-Q stage		●	●	●	●	●	●
Cough stress test		●	●	●	●	●	●
Vaginal relaxity		●	●	●	●	●	●
Pelvic floor electrophysiological test		◎	◎	◎	◎	◎	◎
Pelvic floor ultrasound		◎	◎	◎	◎	◎	◎
Spine X-ray		◎	◎	◎	◎	◎	◎
Body Composition		◎	◎	◎	◎	◎	◎
Hand grip test		◎	◎	◎	◎	◎	◎
Trunk endurance test		◎	◎	◎	◎	◎	◎
Questionnaires	PFDI-20	◯	◯	◯	◯	◯	◯
	PFIQ-7	◯	◯	◯	◯	◯	◯
	FSFI-6	◯	◯	◯	◯	◯	◯
	IPAQ-SF	◯	◯	◯	◯	◯	◯
	PSQI	◯	◯	◯	◯	◯	◯
Training record				✷	✷(if any)		
RPE				✷			
Adverse Event				☐	☐		

●: Data would be collected by pelvic floor professionals via vaginal palpation. ◎: Data would be collected by experienced General specialists as the examiners. ◯: data would be collected by requesting all participants to give answers through scanning a QR code. ✷: Recording by all the participants in EG only per their training record and RPE score given by themselves.: Optional items. Abbreviations: MOS: The modified Oxford Scale [3], which needs to be performed by inserting two fingers into the vagina for approximately 4 cm to feel the FPM contraction and give scale ranging from 0 (no contraction) to 5 (strong contraction).; POP-Q [5]: pelvic organ prolapse quantitation; PFDI-20: The Pelvic Floor Distress Inventory Questionnaire-20; PFIQ-7: Pelvic Floor Impact Questionnaire-7; FSFI-6: The 6-item Female Sexual Function Index; IPAQ-SF; International Physical Activity Questionnaire Score-Short Form; RPE: Ratings of Perceived Exertion.

**Table 3 ijerph-19-11073-t003:** Outline of Soring for general pelvic floor function.

Testing Items	Indicators	Compute Value	Score Value
POP-Q	Stage 0	0	
	Stage I	1	
	Stage II	2	
	Stage III	3	
	Stage IV	4	
Cough stress test	Yes	1	
	No	0	
Vaginal relaxation	≥4 fingers	4	
	>3 fingers, and <4 fingers	3	
	=3 fingers	2	
	>2 fingers, and <3 fingers	1	
	≤2 fingers	0	
Pelvic floor electrophysiological test [40]	<20 cm^2^Hg	1	
	≥20 cm^2^Hg	0	
			* Total Score ^1^
PFDI-20	-	Comprehensive score	
PFIQ-7	-	Comprehensive score	
FSFI-6	-	Comprehensive score	
			* Total Score ^2^

* The total score ^1^ means the sum of all above score values which represents objective indicators for pelvic floor function. The lower the total score, the better the pelvic floor function; the total score ^2^ means the sum of the above three comprehensive score which represents women’s subjective evaluation by themselves for pelvic floor.

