## 3. Data Collection and Management

Demographic data, including the age, height, weight, body mass index (BMI), prenatal maximum weight, physical activity during pre-pregnancy and pregnancy, and background data including the working position, smoking, alcohol consumption, urine leakage, asthma, constipation, family history of PFD, delivery history of pregnancy, weight gain during pregnancy, and fetal weight, would be collected at the enrollment visit of the study; while the following questionnaires would be filled by all participants at baseline and at all follow-up visits: (1)The International Physical Activity Questionnaire Score-Short Form (IPAQ-SF), which were recommended as a cost-effective method to assess physical activity by nine questions recording the activity of four levels of intensities in short forms: vigorous-intensity, moderate-intensity, walking, and sitting [31];(2)The Pelvic Floor Distress Inventory Questionnaire-20 (PFDI-20) and Pelvic Floor Impact Questionnaire-7 (PFIQ-7), which were designed to comprehensively evaluate to what extent the lower urinary tract, lower gastrointestinal tract, and pelvic organ prolapse symptoms affect the quality of life of women who suffer from PFD [32];(3)The Female Sexual Function Index (FSFI-6) [33], a common tool that has been validated for clinical use for evaluating female sexual function in six terms [34,35];(4)The Pittsburgh Sleep Quality Index (PSQI), which was developed in 1989 and accepted as the most common measure of sleep quality [36].

Baseline demographic data, IPAQ-SF, PFDI-20, PFIQ-7, FSFI-6, and PSQI were integrated into a WeChat mini program and can be filled by the Participants themselves by scanning a QR code on WeChat, a social App that is commonly used by the public in China. The body mass index (BMI) among the demographic data and all the scores or grades for all the questionnaires can be automatically come out by the configured formulas in the WeChat mini program. 

Following the questionnaires in each of the visits would be the physical examination including PFM strength evaluation by Modified Oxford Grading (MOS) [3], pelvic organ prolapse quantitation (POP-Q) stage [5], vaginal relaxtity, symptomatic SUI detection and grading, pelvic floor surface electromyography (sEMG) based on Glazer protocol [37], pelvic floor ultrasound examination, quantitative measurement of pelvic sagittal rotation degree by X-ray, and evaluation of the overall body composition and strength. 

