Pelvic floor surface electromyography (sEMG) would be tested based on Glazer protocol. The participants would be taught to contract the pelvic floor muscle correctly and will have one practice before testing.

SUI is defined by SUI symptoms or a positive result of the cough stress test. Before the cough stress test, participants are suggested to keep fully bladder. Positive result of the test is defined as involuntarily urinary leakage when asked to cough in the lithotomy position.

Pelvic floor ultrasound indicators, which include LAM thickness, diameter of the levator hiatus, and levator hiatus area, were measured using the proprietary software 4D View via transperineal ultrasound(GE Kretz Medizintechnik), a reproducible and reliable measurement of vaginal support [38].

The quantitative measurement of pelvic sagittal rotation degree on Spine X-ray (Definium7000, General Electric Company, Boston, MD, USA) was analyzed which includes the pelvic tilt angle, the sacral slope angle, the difference of sacral slope and pelvic tilt, the ratio of the pelvic tilt angle to the sacral slope angle, the ratio of the pelvic tilt angle to the pelvic incidence angle and sacral-femoral distance.

The change of the overall body composition would be analyzed through body composition analyzers (Inbody 770), and overall strength which would be measured through hand grip strength test and trunk endurance test. Body composition analyzers would analyze data regarding waist hip ratio, basal metabolic rate, body fat rate, etc. Hand grip strength would be measured by JAMAR Plus+ grip gauge. The measurement accuracy is 0.1 kg. The participants should not have visible hand defects. The grip gauge should be adjusted before measurement. When the participants hold the grip gauge, the second knuckle of the index finger should be at 90 degrees. At the same time, mark the best position of each hand on the grip meter. Before measurement, the participants should remove wrist jewelry to avoid injury. The left and right hand are measured alternately three times. Trunk endurance would be tested using the Plank test, Side bend test, and Biering–Sorensen Test [39]. All the participants were encouraged to keep the positions as long as possible. Time as recorded in seconds with a maximal length of 90 s.

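### Table 3's Total Score 2 adds a sexual-function score to two symptom-burden scores with no stated reversal, scaling or direction; separately, one item of Total Score 1 carries a unit that does not fit its test

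*Protocol article*

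**What the plan says.** Table 3 of the protocol article sets out a scoring scheme for general pelvic floor function with two totals.

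- **Total Score 2.** PFDI-20, PFIQ-7 and FSFI-6 each enter as a comprehensive score. The footnote says that this total "means the sum of the above three comprehensive score" and that it stands for the women's own assessment. It gives no reversal, scaling or direction for this total.
- **Total Score 1.** The footnote reads: "The total score ^1^ means the sum of all above score values which represents objective indicators for pelvic floor function". The items are POP-Q stage (0 to 4), cough stress test (0 or 1), vaginal relaxation (0 to 4) and the electrophysiological test (0 or 1). For this total a direction is given: "The lower the total score, the better the pelvic floor function". The electrophysiological item scores 1 below 20 and 0 from 20 upwards, with the unit printed as cm²Hg in both rows.

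Section 3 (Data Collection and Management) describes the instruments. PFDI-20 and PFIQ-7 are there to "comprehensively evaluate to what extent the lower urinary tract, lower gastrointestinal tract, and pelvic organ prolapse symptoms affect the quality of life". FSFI-6 is "a common tool that has been validated for clinical use for evaluating female sexual function in six terms". On the electrophysiological test it says: "Pelvic floor surface electromyography (sEMG) would be tested based on Glazer protocol".

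Section 4 (Outcomes of the Study) makes MOS the primary outcome and numbers five secondary outcomes. Neither total is among them. Table 3 is mentioned there only as part of the list of data collection instruments.

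**The concern.** A sum can be read only if all its parts point the same way. By name and description, two parts of Total Score 2 measure burden and one measures function. Added without reversal, a gain in sexual function and a rise in distress push the total in the same direction. A reader shown a lower mean in one arm could not tell whether those women had fewer symptoms or poorer sexual function. Because no direction is declared for this total, one could also be chosen after the data are seen.

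The unit in Total Score 1 is a smaller and separate matter. Surface EMG records an electrical signal, whereas the printed unit resembles one of pressure. The number 20 is clear, but the quantity it applies to is not.

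**Working it through.** The article gives no range, worked value or direction for Total Score 2, so there is no stated figure to reproduce. The power in Section 4.1 rests on MOS improvement proportions and does not involve Table 3.

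**1. Direction of Total Score 2.** Write D for PFDI-20, I for PFIQ-7 and F for FSFI-6.

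- As printed: S = D + I + F, so change in S = ΔD + ΔI + ΔF.
- With FSFI-6 reversed: change in S′ = ΔD + ΔI − ΔF.

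The changes below are illustrative and do not come from the article. Improvement means D and I fall and F rises.

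| ΔD | ΔI | ΔF | Printed sum | FSFI-6 reversed |
|---|---|---|---|---|
| −5 | −3 | +8 | −5 − 3 + 8 = 0 | −5 − 3 − 8 = −16 |
| −5 | −5 | +10 | −5 − 5 + 10 = 0 | −5 − 5 − 10 = −20 |
| 0 | 0 | +10 | +10 | −10 |
| 0 | 0 | −10 | −10 | +10 |

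In the first two rows everything improves and the printed total does not move. In the third, only sexual function improves and the total rises, as it would with worse distress.

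**2. How much the fault matters depends on the scale ranges, which the article does not give.** Suppose a woman improves by the same fraction p of the range on all three scales.

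- *Assumption A, equal ranges R:* printed change = −Rp − Rp + Rp = −Rp; with reversal −3Rp. FSFI-6 supplies one third of the total's range, and two thirds of the signal is lost.
- *Assumption B, PFDI-20 and PFIQ-7 each spanning 300 and FSFI-6 spanning 28:* FSFI-6 supplies 28/628 = 4.5% of the range. Printed change = −(300 + 300 − 28)p = −572p; with reversal −628p. Since 572/628 = 0.911, about 9% is lost. With an FSFI-6 span of 30 the share is 30/630 = 4.8%, and 570/630 = 0.905, so about 10% is lost.

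The size of the fault therefore varies widely. In both cases FSFI-6 has the wrong sign; under B it is also nearly swamped, which is why reversal without scaling is not enough.

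**3. Total Score 1.**

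- Maximum = 4 (POP-Q) + 1 (cough) + 4 (vaginal relaxation) + 1 (electrophysiology) = 10.
- The item with the doubtful unit supplies 1/10 = 10% of the maximum; the other 9 points do not depend on it.
- All four items, including the electrophysiological one as coded, run higher = worse, which agrees with the footnote.
- Section 3 lists surface EMG and no other electrophysiological test; Table 2 lists an electrophysiological test and no separate EMG. They are taken here to be the same test.

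**The case against.** Several points on the other side have force.

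- **The article states no scoring direction for any questionnaire.** This is correct: the directions used here are inferred from names and descriptions. Section 3 also says that the scores are produced by formulas in a WeChat mini program that is not shown, so a hidden reversal of FSFI-6 cannot be excluded. But the footnote defines the total as a sum and mentions no reversal, so the rule as published is still faulty.
- **The exact cancellation is constructed.** It is. Under Assumption B the two burden scores dominate and full cancellation would be unusual. What stands is the wrong sign and the missing direction.
- **The totals may never be compared between arms.** Section 4.2 names no analysis of them, and Section 4 says the other secondary measures in Table 2, which lists all three questionnaires, are to be calculated and discussed separately. A reader might infer that the second hypothesis in the Introduction (benefit on overall function) rests on Table 3, and that a group comparison is therefore biased towards no effect. The article does not support this: that hypothesis does not cite the table, and no such comparison is specified.
- **The unit may be a printing slip.** It may, and Table 3 cites a source for the test that is not at hand. The printed unit still points to pressure while Section 3 describes EMG, so the two places need reconciling. A reader might go further and conclude that Total Score 1 cannot measure pelvic floor function either. That does not follow, because the fault touches one binary item and the other three are consistently coded.

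**Conclusion.** The point holds in a limited form. As defined in Table 3, Total Score 2 has no interpretable direction, because a function score is added to two burden scores without stated reversal, scaling or direction. The conclusion assumes that PFDI-20 and PFIQ-7 run higher = worse, that FSFI-6 runs higher = better, and that no reversal is built into the unseen formulas. If all three scales improve by the same fraction of their range, the lost signal runs from about 9% to two thirds across the assumed ranges.

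The electrophysiological unit is a separate correction affecting at most 1 of 10 points; Total Score 1 is otherwise sound. MOS as primary outcome, the sample size and the five numbered secondary outcomes are untouched. This should be corrected before analysis, but it does not threaten the trial's main result.

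**What to change.** 1. Do not use the raw sum. Analyse PFDI-20, PFIQ-7 and FSFI-6 separately, stating the direction of each.
2. If a single index is kept, reverse FSFI-6, standardise each score before combining (for example by its baseline standard deviation), and state in the footnote that lower is better. If the questionnaire software already reverses FSFI-6, say so.
3. In Table 3, state what the electrophysiological item measures and in what unit, so that it agrees with the surface EMG description in Section 3.

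The cost is a change to one table, its footnote and a sentence of text. The data collected stay the same. The change should be dated before the data are analysed, so that the scoring direction is not chosen after results are known.
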